#### Sample size estimation

The sample size calculations are based on two of the key findings from our pilot data: (1) mean CGM glucose; (2) glucotype. For the first a sample size of 280 women, will give 28 women who have LGA and 252 who do not, with a 90% power to detect a difference in glucose of 0.4 mmol/l with a SD of 0.6 at p = 0.05. This is a clinically relevant effect size in pregnancy. This has been illustrated in HAPO [8] with an OR 1.38 (1.32–1.44) for birthweight > 90th centile, with an increase in glucose of 0.4 mmol/l; A similar effect size was seen in CONCEPTT [26] and previous CGM analysis in pre-gestational diabetes [24, 29, 30]. Furthermore, improving CGM glucose by this small, but clinically relevant, amount in pregnancy is significantly associated with improved clinical outcomes, including LGA [26]. To ascertain the exposure of severe glucotype to LGA a sample size of 384 women, will give 38 women with LGA, and 346 who do not, with 90% power to detect a difference in glucotype (based on the prevalence of severe glucotype in the non LGA group of 37%, and in the LGA group of 64%). As GDM diagnosed by OGTT has a prevalence of 10%, then the sample sizes for this outcome, with these two exposures, are the same as for LGA. Allowing for ~ 30% drop out (including miscarriage and/or incomplete data capture) 500 recruits will be needed.

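### 500 recruits with 30% loss leave 350 women, not the 384 needed, so power for the glucotype comparison is about 88% and not the stated 90%

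*Protocol article*

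**What the plan says.** All the figures are in the section on sample size estimation in the protocol article. It sets two requirements, both before any losses.

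- Mean CGM glucose, sized at the 5% level and 90% power on a 0.4 mmol/l difference (SD 0.6): "a sample size of 280 women, will give 28 women who have LGA and 252 who do not".
- Severe glucotype: "a sample size of 384 women, will give 38 women with LGA, and 346 who do not, with 90% power". The assumed prevalence of severe glucotype is 37% without LGA and 64% with LGA.

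The section extends both numbers to the maternal primary outcome: "As GDM diagnosed by OGTT has a prevalence of 10%, then the sample sizes for this outcome, with these two exposures, are the same as" those of the neonatal one. It then closes with the recruitment target: "Allowing for ~ 30% drop out (including miscarriage and/or incomplete data capture) 500 recruits will be needed". The article gives no other figure for expected loss.

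**The concern.** The larger requirement, 384 women, must be met after losses, because women who miscarry or have too little data do not enter the comparison. To allow for a loss fraction d, the analysable number is divided by 1 − d. The stated target looks as if it was obtained by multiplying by 1 + d, which always gives too few.

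If so, the 90% power for glucotype does not hold at the loss rate the section itself expects. The margin for loss is also misstated. A team that tracks attrition against 30% would think itself on plan at 28%, when the analysable number would already be below 384.

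**Working it through.** **Inputs, all from the sample size section.** 384 women (38 LGA, 346 not); severe glucotype 64% and 37%; power 90%; loss about 30%; 500 recruits; 280 women (28 and 252), difference 0.4 mmol/l and SD 0.6 for mean glucose. Significance level 0.05 is stated for mean glucose and assumed here to apply to glucotype as well. Sidedness is not stated; a two-sided test reproduces the plan's figure.

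**Step 1: reproduce the 384.** Two-proportion test with pooled variance under the null and no continuity correction:

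power = Φ[(|p1 − p2| − 1.96 × SE0) / SE1], where SE0 = √[p̄(1 − p̄)(1/n1 + 1/n2)] and SE1 = √[p1(1 − p1)/n1 + p2(1 − p2)/n2].

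With n1 = 38 and n2 = 346: p̄ = 0.3967, SE0 = 0.0836, SE1 = 0.0821. Power = Φ[(0.27 − 1.96 × 0.0836) / 0.0821] = Φ(1.293) = 90.2%. Exact enumeration of the same test gives 90.0%. Solving for the sample size at this ratio returns 38 LGA women and 384 in total. The base number is sound.

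**Step 2: the allowance for loss.**

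| Calculation | Result |
|---|---|
| 384 / (1 − 0.30) | 548.6, so 549 recruits |
| 384 × 1.30 | 499.2, so 500 recruits |
| 500 × (1 − 0.30) | 350 analysable |
| 1 − 384/500 | 23.2% tolerable loss |

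The smaller requirement does not explain the target: 280 / 0.7 = 400 and 280 × 1.3 = 364. The gap is 549 − 500 = 49 recruits, or 384 − 350 = 34 analysable women (34/384 = 9%).

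**Step 3: power for glucotype at the stated loss.** With 10% LGA, 350 women split into 35 and 315: p̄ = 0.3970, SE0 = 0.0872, SE1 = 0.0856. Power = Φ[(0.27 − 1.96 × 0.0872) / 0.0856] = Φ(1.159) = 87.7%. Exact enumeration gives 87.6%.

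Power for 500 recruits at other loss rates, with 10% LGA:

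| Loss | Analysable | Power |
|---|---|---|
| 23.2% | 384 | 90.5% |
| 25% | 375 | 89.8% |
| 28% | 360 | 88.6% |
| 30% | 350 | 87.7% |
| 35% | 325 | 85.2% |

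The first row uses an exact 10% split (38.4 and 345.6), hence 90.5% and not the 90.2% of step 1.

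**Step 4: power for mean glucose.** A t test for 0.4 mmol/l with SD 0.6 gives 91.5% power at 28 and 252, and 96.2% at 35 and 315. This comparison keeps its 90% and, with 500 recruits, would tolerate a loss of 1 − 280/500 = 44%.

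**The case against.** The strongest reply is that the effect is small. Power falls by about 2.5 points, for one of the two exposures used for sizing, in an observational cohort, and nothing in recruitment or analysis has to change. The loss is only approximate, and at 25% power is already 89.8%. The result also depends on an outcome prevalence of exactly 10%: if it were 11% (an assumption, not a figure from the article), 350 women would include about 38.5 cases and power would be 90.2%. Finally, the article shows no inflation formula, so the multiplication by 1.3 is inferred.

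Much of this stands. The shortfall is modest, it concerns glucotype only, and the cause is an inference from a close numerical match. The number analysable for GDM may also differ from that for LGA, since one outcome is determined at the OGTT and the other at birth; using one number for both is the article's own simplification.

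None of it reconciles the figures. A loss of 23.2% would not normally be described as about 30%. A higher prevalence is not what the plan assumes. The contradiction between 384, about 30% and 500 stands however 500 was reached, and it does not depend on anything left to a fuller document.

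**Conclusion.** The point holds. The section's 384 analysable women, loss of about 30% and 500 recruits do not agree. At 30% loss, 350 women remain and power for the glucotype comparison is 87.7%, against 90% stated. The same applies to GDM, because the section assigns it the same sample sizes. The mean-glucose comparison is adequately powered, and the study remains viable.

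The result assumes a two-sided 0.05 test without continuity correction (the version that reproduces 384), a 10% outcome prevalence, and loss that does not depend on outcome. The error is small in power, but it is plain arithmetic in the sentence that justifies the recruitment target, and it overstates how much attrition the study can absorb.

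**What to change.** Keep 500 and correct the closing sentence of the sample size section in one of two ways:

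- state that 500 recruits yield 384 analysable women provided loss does not exceed 23%; or
- state that with 30% loss, 350 women (35 with LGA) give about 88% power for the glucotype comparison and about 96% for a 0.4 mmol/l difference in mean glucose.

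Use the same figures for GDM, in line with the section's assumption of equal prevalence. If 90% power for glucotype at 30% loss is really intended, the target is 549.

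Either rewording costs one sentence and no extra recruits; the stated power or the stated margin for loss becomes slightly less favourable. Raising the target would cost 49 more recruits.

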#### Trial management

University of Leeds is the study sponsor and has delegated responsibility for the overall management of the study to the chief investigator, including the design, coordination, monitoring and analysis and reporting of results. A Study Steering Committee SSC has been set up to assist with developing the design, co-ordination and strategic management of the study.

#### Data management

Data and statistical analyses will be handled by the University of Lincoln, in conjunction with the University of Leeds, United Kingdom.

## Discussion

This study will provide an extensive number of individual glucose measurements which will ascertain the relationship of maternal dysglycemia to fetal growth and outcomes. It will explore whether CGM glucose profiling can detect GDM before the OGTT; or indeed whether CGM glucose profiling may be more useful than the OGTT at detecting LGA and other perinatal outcomes. This data will be relevant to inform future NICE and International guidelines on how best to screen and detect GDM using CGM.

## Data Availability

Requests for access to study data and stored samples will be considered, and approved in writing where appropriate, after formal application to the SSC. Inquiries for data should be addressed to the principal investigator [name] [name].

## List of abbreviations

BMI: Body Mass Index
CGM: Continuous glucose monitoring
FDA: Functional data analysis
GDM: Gestational diabetes
GROW: Gestation related optimal weight
HbA1c: Haemoglobin A1c
HAPO: Hyperglycaemia and adverse pregnancy outcomes
HRA: Health research authority
LGA: Large for gestational age
NICE: National institute for heath and care excellence
NHS: National health service
NICU: Neonatal intensive care unit
OR: Odds ratio
OGTT: Oral glucose tolerance test
SD: Standard deviation
SGA: Small for gestational age
SSC: Study steering committee
T2DM: Type 2 diabetes mellitus
T1DM: Type 1 diabetes mellitus
USS: Ultrasound scan
